### Procedure

Participants will be recruited from the medical oncology, radiation oncology and haematology outpatient clinics from three major cancer centres in NSW, Australia. Initially, a research nurse will review clinic lists to identify patients who meet eligibility criterion (1). The list will then be reviewed by a clinician or clinic nurse to exclude patients who do not meet eligibility criteria (2), (3) and (4) and to make the initial approach to eligible patients. The research nurse will then provide a verbal and written explanation of the study to patients interested in the study and obtain their informed consent to participate. Consenting participants will be asked to nominate a caregiver and if the caregiver is present at the clinic at the time of recruitment, the research nurse will provide them with a verbal and written explanation of the study. If not, the caregiver information will be given to the patient who will be asked to pass it on to the caregiver. If the patient is unable to nominate a caregiver at the time of recruitment, s/he will be asked during the first and subsequent computer assisted telephone interviews (CATIs) to nominate a caregiver in case their circumstances change during the course of the study.

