#### Intervention resources

The *Guidelines *include reviews of the current referral practices and utilisation of palliative care services in Australia; patients' physical, psychological, social/cultural, spiritual and financial/legal issues; as well as caregivers/families' and health professionals' issues [6].

The NAT: PD-C aims to operationalise the *Guidelines *and includes four sections:

1. Section 1 includes three items to fast-track a review by a specialist palliative care service: the absence of a caregiver (if one is needed), a patient or caregiver request for referral to a specialist palliative care service, and the health professional's need for assistance in managing care;

2. Section 2 assesses the patient's wellbeing, and includes physical, daily living, psychological, information, spiritual/existential, cultural and social, financial and legal domains;

3. Section 3 assesses the ability of the caregiver/family to care for the patient, and includes physical, daily living, psychological, information, financial and legal and family and relationship domains;

4. Section 4 assesses the caregiver's own wellbeing, including physical, psychological and bereavement issues.

For Section 1, response options are "Yes" or "No". Items in Sections 2-4 are assessed according to the level of concern ("none", "some/potential for", "significant") they were causing. Prompt questions for each item were included on the back page, to facilitate consistency in how issues were addressed. Each item has a set of tick boxes to indicate the action taken ("directly managed", "managed by another care team member", "referral required") to address any identified needs. Finally, should a referral be required, the NAT: PD-C includes a section detailing the type of referral made (eg to specialist palliative care service, social worker, general practitioner, medical oncologist), the urgency of the referral ("urgent", "semi-urgent", "non-urgent") and client knowledge of the referral.

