### Analysis

Descriptive statistics of patient characteristics at baseline and summary measures of their level of need, anxiety, depression and quality of life at each time point will be presented as means and 95% confidence intervals for continuous variables and as proportions and 95% confidence where the data were categorical. The patients' baseline interview scores for each of these outcomes will be examined to determine whether scores varied according to age, gender, presence of a caregiver and level of care giving provided to them. Statistical significance will be assessed using chi square tests for categorical variables and t-tests for continuous outcomes (α = 0.05).

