#### Changes in primary and secondary outcomes over time

For each patient, level of need, anxiety, depression and quality of life will be measured repeatedly during the study and therefore a Generalised Estimating Equation (GEE) model will be used to analyse the data [39]. In this study the GEE model will fit time as a factor and also analyse the number of CATIs completed as an interaction variable. Age, gender, time since diagnosis, co-morbidity score and presence of a caregiver will be included as potential confounding variables for patient participants. Age and gender will also be included as confounder for caregiver participants. For the purpose of this study, presence of a caregiver will include patients who had a participating caregiver at first assessment as well as patients who subsequently indicated they had a caregiver in any of their CATIs (irrespective of whether their caregiver consented to participate). GEEs will be run for both continuous and categorical outcome variables adjusting for the potential confounders listed above to ascertain whether the intervention had any impact on patient and caregiver outcomes.

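### The adjustment covariate for caregiver presence is set by any interview during follow-up, so it uses later answers and depends on how many interviews the patient completes

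*Protocol article*

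**What the plan says.** Under Changes in primary and secondary outcomes over time, the protocol article lists the adjustment variables: "Age, gender, time since diagnosis, co-morbidity score and presence of a caregiver will be included as potential confounding variables for patient participants". It then defines the last one in two parts. The first part counts a patient whose caregiver was already taking part when the patient was first assessed. The second part adds "patients who subsequently indicated they had a caregiver in any of their CATIs (irrespective of whether their caregiver consented to participate". Nothing limits the second part to baseline or pre-intervention interviews, and nothing makes the variable change over time.

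The definition opens with "For the purpose of this study, presence of a caregiver will include", so it reads as applying throughout. The opening paragraph of Analysis uses the same variable at baseline, to "determine whether scores varied according to age, gender, presence of a caregiver and level of care giving provided to them".

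Under Procedure, a patient who cannot name a caregiver at recruitment is "asked during the first and subsequent computer assisted telephone interviews (CATIs) to nominate a caregiver in case their circumstances change". The Abstract gives interviews every two months for up to 18 months, with the intervention introduced after at least two of them.

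**The concern.** A covariate used to remove confounding, or to form groups at baseline, should be known when the record it adjusts is made. Here a caregiver first reported late in follow-up relabels all of the patient's records, including those before the intervention.

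Each further interview is also another chance to acquire the label. The patients have incurable cancer, so the number of interviews completed probably reflects prognosis, and the label then carries prognosis with it. At stake are the caregiver coefficient in the GEE models and the baseline comparison by caregiver presence. Either could show a protective association that the definition itself produced.

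**Working it through.** **Inputs from the article.** Interviews every 2 months for up to 18 months give about 18/2 = 9 per patient at most. At least two precede the intervention, so up to seven of nine follow it. Sample size gives 50% pre-intervention prevalence of need, and 60% of 407 patients with a consenting caregiver (0.60 × 407 = 244.2; stated as 245). The 407 itself reproduces to within 1: 50% against 40%, two-sided 5%, 80% power and continuity correction give 408. This point does not depend on it.

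**Assumptions.** The article does not give b, the share with a caregiver at first assessment, or q, the chance per later interview that a patient without one first reports one. I take b = 0.60, using the consenting share as a stand-in, and q = 2%, 5% and 10%.

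**Step 1: the label against interviews completed.** For k interviews, P(labelled present) = 1 − (1 − b)(1 − q)^(k−1).

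| q | k = 1 | k = 3 | k = 5 | k = 9 |
|---|---|---|---|---|
| 2% | 60.0% | 61.6% | 63.1% | 66.0% |
| 5% | 60.0% | 63.9% | 67.4% | 73.5% |
| 10% | 60.0% | 67.6% | 73.8% | 82.8% |

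The rise from one to nine interviews is 6 to 23 percentage points. With b = 0.80 the share at k = 9 is 83.0%, 86.7% and 91.4%. Status fixed at first assessment does not vary with k.

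**Step 2: what this does to the estimates.** I simulated 200,000 patients with a standard normal severity u. The log-odds of need is g·u and the chance of leaving after each interview is expit(−2.2 + g·u), with g = 0.8 and at most nine interviews. Caregiver status has no effect on need. The model is logistic with an independence working correlation, a caregiver term and a pre/post term (first two interviews against the rest). The Monte Carlo standard error of the baseline difference is about 0.2 points.

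| q before / after intervention | Baseline need, present minus absent, label from any interview | Caregiver OR, label from any interview | Pre/post OR: first-assessment label, then label from any interview |
|---|---|---|---|
| 2% / 2% | −0.6 points | 0.99 | 0.810, 0.810 |
| 5% / 5% | −1.8 points | 0.96 | 0.810, 0.811 |
| 10% / 10% | −3.7 points | 0.93 | 0.811, 0.814 |
| 2% / 10% | −3.5 points | 0.92 | 0.568, 0.571 |

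With the first-assessment label, the baseline difference was within 0.2 points of zero and the caregiver OR within 0.005 of 1. The last row includes an intervention effect of −0.4 on the log-odds. In the first three rows there is none; the pre/post OR is below 1 under both labels only because sicker patients leave.

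The size depends on g. From g = 0.5 to 1.0 the baseline difference runs from −1.2 to −2.8 points at q = 5%, and from −2.4 to −5.4 points at q = 10%. The largest pre/post change in those runs was 0.005.

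**Step 3: an adverse case.** The intervention is now allowed to raise caregiver acquisition, and caregivers strongly reduce need (−0.8 on the log-odds). With q = 2% before and 10% after, the pre/post OR moves from 0.515 to 0.535. With 2% and 15% it moves from 0.493 to 0.519. Two other runs with a strong caregiver effect, and acquisition of 2–5% before and 10–15% after, gave 0.517 to 0.531 and 0.510 to 0.529. The shift is about 0.02 (0.014 to 0.026), towards no effect.

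**The case against.** The case for leaving this alone has four parts.

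- **It is a nuisance covariate.** The trial asks about change from before to after the intervention. A label that is constant within a patient takes the same value on both sides, so it can absorb little of that change. This stands, and the pre/post results above agree with it.
- **Later reports may correct the record.** The first part of the definition counts only participating caregivers, and a caregiver absent from the clinic is reached only through the patient. Some later reports will reveal a caregiver who was there all along. This stands, and it means that the assumed q overstates true change for some patients.
- **The model includes the number of completed interviews as an interaction variable.** This may absorb part of the link with follow-up length. It does not remove the use of later answers, and it does nothing for the baseline comparisons.
- **The baseline comparison is descriptive.** True, but it is to be tested at α = 0.05, and a label set months later does not describe baseline.

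Stronger readings are tempting. One is that the plan adjusts away part of the intervention's effect, because the NAT: PD-C records "the absence of a caregiver (if one is needed". The article says only that this item fast-tracks a specialist palliative care review. It does not say that the tool or the service supplies a caregiver, so the route is possible but not shown. Another is to call this immortal-time bias. There is no time-to-event outcome, the article does not mention survival here, and leaving for any reason acts the same way. A third is that most patients without a caregiver would be reclassified. At q = 10%, 1 − 0.9^8 = 57% of them would be after eight further interviews, but that is 0.40 × 57% = 23 points of all patients, and only among those who complete all nine.

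**Conclusion.** The concern holds in a limited form. The rule is stated, not left open: caregiver presence is fixed from any interview, so it depends on later answers and on the number of interviews completed. If sicker patients complete fewer interviews, it produces a false association with lower need. That association is about 2 to 4 percentage points at baseline and a caregiver OR of about 0.92 to 0.96, where reporting reaches 5–10% per interview either throughout or only after the intervention. It is under 1 point at a constant 2%, and larger if severity drives both need and drop-out more strongly. These rates, b and g are assumptions.

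The documents do not support a claim of material bias in the intervention effect. The pre/post OR changed by 0.001 to 0.003 in the central settings with acquisition of 5% or more, and by about 0.02 when the assumptions were chosen to be adverse. The definition should be corrected because the caregiver estimates and baseline comparisons would otherwise be misread, not because the main comparison is at risk.

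**What to change.** Define presence of a caregiver, for both the baseline comparisons and the GEE adjustment, as any caregiver reported at recruitment or at the first interview, whether or not that caregiver takes part. This keeps the plan's sensible intention of counting non-participating caregivers. Report later changes in status descriptively, by interview, and do not use them for adjustment: status after the intervention starts could lie on the intervention's own pathway.

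The cost is one sentence. Procedure already has patients without a nominated caregiver asked at the first interview, so no new data are needed and the sample size is unchanged. The downside is that a caregiver who existed but was not mentioned by the first interview is classified as absent.

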#### Feasibility and acceptability of the *NAT*: PD-C

The uptake of the NAT: PD-C will be examined within the outpatient clinic setting by comparing the number of NAT: PD-Cs due for completion for each patient during the study (depending on the regularity of their appointments) with the number of NAT: PD-Cs that were actually completed. The impact of completing the NAT: PD-C on length of consultation in outpatient clinics will also be examined by audio-taping consultations in which the NAT: PD-C was completed and others in which it was not completed.

#### Service utilisation and referral patterns

The date of completion of each NAT: PD-C; the levels of need recorded on each NAT: PD-C; and the actions taken to meet identified unmet needs (including referrals to health professionals and/or services) will be identified. Using self-report CATI information, the mean number of health professionals to whom referrals were suggested at each time point pre- and post-intervention will be determined. Any change in the number of health professionals seen over time will be assessed using GEEs. Each patient's medical record will be audited to determine the dates of referral to health professional/services and dates on which the patient was seen by these health professional/services.

## Discussion

This study will assess whether the use of the Guidelines and NAT:PD-C will prompt a more comprehensive assessment of patient and caregiver concerns, potentially bringing about a reduction in the level of unmet needs, depression and anxiety; as well as an increase in patient quality of life. Moreover, it is hoped that these resources will prompt health professionals to address these unmet needs in a timely and appropriate manner either themselves or through referrals to other care team members or specialist providers. The study will examine the feasibility and efficacy of routine, systematic and regular use of the Guidelines and NAT: PD-C in a range of clinical settings in terms of their ability to facilitate the timely provision of needs based care for people with advanced cancer.
